**Secondary Outcomes**

Efficacy will be assessed using measures for muscle strength, mobility, functional status, quality of life, and discharge destination. The primary outcome for efficacy will be lower extremity **muscle strength**.

**1. Lower extremity muscle strength.** Lower extremity muscle strength will be measured using the time to perform one sit-to-stand (42, 43). Time to perform one sit-to-stand has good validity and reliability. The ability to perform one sit to stand has been used in a study involving sit-to-stand activity with older adults with dementia in nursing homes (31). Repeated observations of the sit to stand test by one observer yielded correlations of 0.89 to 0.96 (44).

Older adults who are frail, such as those who are in nursing homes, must use their arms to stand and may be unable to complete more than one sit to stand (45). For a study involving sit-to-stand activity with older adults with dementia in nursing homes, participants were asked to stand from a seated position three times, with the time to complete the sit to stand measured at the third time using a stopwatch (31, 45) (personal communication with [name] January 16, 2023). Similarly, for the present study, the interventionist or RA will ask participants to stand from a seated position three times, with the time to complete the sit to stand measured at the third time using a stopwatch (Appendix E). The interventionist and the RAs will measure the time to complete the sit to stand for participants until ≥75% interrater agreement is reached (46). Then only one RA or the interventionist will collect the rest of the outcome measures data.

**2. Mobility.** Mobility will be measured using the two-minute walk test (2MWT). The 2MWT has good validity and reliability. It has been used in studies involving older adults with dementia in nursing homes (23, 34). As well, the 2MWT has been shown to provide sufficient data to objectively quantify gait measurements, similar to the six-minute walk test (47). The 2MWT has a test-retest reliability coefficient of 0.98 (0.96–0.99) and an inter-rater reliability of 0.92 (0.86–0.96) when assessed in frail older adults with dementia (34). Distances walked for the 2MWT among older adults with dementia in nursing homes and day care centers ranged between 63.1-63.6 meters (34). The minimal detectable change (MDC), that is, the minimum change that is considered a true change in performance, for the 2MWT is 9.1 meters (34).

The testing procedure for the 2MWT to be used will be similar to the ones used in studies involving older adults with cognitive impairment in nursing homes (34, 48) (Appendix E).

**3. Functional status.** Functional status will be measured by the Barthel Index (BI) (Appendix E), which has been shown to have a good reliability (kappa > 0.75) and validity for short stay older adult patients (49) and has acceptable item reliability (1.0) and person reliability (0.88) in older adults with dementia (50). BI is a 10-item questionnaire which is scored out of 20, with higher scores meaning a better outcome. A change in BI score of 1 point is considered a meaningful change in a person’s level of independence (35). When the BI score is multiplied by 5, a score of 0-20 indicates total dependency, 21-60 indicates severe dependency, 61-90 indicates moderate dependency, and 91-99 indicates slight dependency (51). BI scores will be measured at pretest, time 2, and post-test.

**4. Quality of life.** Quality of life will be measured using the QOL-AD Quality of Life–Alzheimer’s Disease, a 13-item questionnaire that asks about physical health, energy, mood and other quality of life measures that can be answered by older adults with CI (52). The QOL-AD has good reliability (α from 0.83 to 0.90) and validity correlation with measures of depression (r = −0.41 to −0.65) (52). A study involving a walking program for older adults with CI in nursing homes resulted in significant improvements to self-reported QOL-AD (27). It takes about 10 minutes to complete the QOL-AD (53). The QOL-AD will be completed by the SDM if the patient is not able to complete it.

5. Satisfaction. Participant satisfaction will be determined using the Client Satisfaction Questionnaire (CSQ) (54), with the cover page for the questionnaire tailored to the TCP setting, which includes 8 Likert scale questions, a comments section; and three open ended questions as was used in the work by Sano and colleagues (33) (Appendix G). As well, qualitative data in the form of field notes will also be taken on interventionists’ report of challenges, issues, and ease of intervention delivery (41). Field notes taken within the intervention fidelity checklist (Appendix S) will also capture interventionists’ perspectives on elements of the intervention that are satisfactory to participants and their care partners. The CSQ will be completed by the SDM if the patient is not able to complete it.

**5. Discharge destination.** Planned and actual discharge destinations will be determined by the interventionist through a chart review or confirmation with TCU staff.

**Additional Data Collected.** At Time 3, the RA will review the participant’s chart to document services provided to the participants in addition to the OASIS Walking Intervention, to increase the internal validity of the study. A shortened version of a checklist of services/treatments related to mobility (Table 3 below) provided to patients in transitional care program developed by [name] and colleagues based on their scoping review on transitional care programs (7) will be completed for this study.

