Target Number of Sit to Stands. The interventionist or RA will measure the number of sit to stands that a participant can do in 30 seconds at baseline. The procedure for this test is outlined in Appendix B and is adapted from the procedure used in previous study (84). Based on that number, a target number of sit to stands to do per session will be determined, based on the algorithm used in the study by Slaughter and colleagues (48). Halfway into the intervention (after 3 weeks), the target number of sit to stands will be progressed. The target number of sit to stands and the algorithm used by Slaughter et al. (48) (Personal communication with [name] January 2023) is outlined in the following formula:

Target number of sit to stands per occasion = (Number of sit to stands done in 30 seconds at baseline +1)

Number of occasions per day = 2 occasions on day shift + 2 occasions on evening shift = 4

Target number of sit to stands per day = 4 x (Number of sit to stands done in 30 seconds at baseline +1)

In the Slaughter et al. study, the adherence to the sit to stand activity was much lower than what was targeted; the average enactment was two sit to stands per day (rather than the target of four) and three sit to stands per occasion (rather than the target of five), for an average of six sit to stands done per day per participant (48).

For this study, the interventionist will meet with participants for one session per day, 5 days per week. Based on the above algorithm and taking into consideration the actual enactment (48), the target number of sit to stands per session for the present study was calculated. The final target number (as calculated by Slaughter and colleagues) will be the same as the progressed target number for the second half of this intervention study (for weeks 4-6); the final target number (as calculated by Slaughter and colleagues) will be multiplied by ½ to form the target for weeks 1-3 of the present study. The algorithm for the present study is outlined in the following formula:

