**Outcome Data Collection Method**

T1, T2, and T3 data will be recorded on paper forms by the RA or interventionist and will be entered on at least a weekly basis into a secure one drive storage database hosted in an iDAPT network for the EnCOAR Team (TRI-UHN), which has restricted access and safety backup. Data on intervention fidelity and adherence will be collected on paper forms by the interventionist immediately after each session with the participants and will be transcribed onto the one drive on a weekly basis.

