**Measures to be taken to Minimize Bias**

Research assistants will be hired and will be trained to collect data from older adults and the procedures will be standardized to minimize bias. Reliable and valid measures have been selected and have well established outcome measures to minimize biases. Patients are selected to participate based on strict inclusion criteria which will minimize sampling bias.

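### Self and SDM answers on the QOL-AD can be mixed within one participant's change, SDM and patient CSQs can be pooled, and the interventionist is allowed to measure the outcomes of the sessions they deliver

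*Protocol*

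**What the plan says.** **Who answers.** Under Secondary Outcomes, for quality of life: "The QOL-AD will be completed by the SDM if the patient is not able to complete it". For satisfaction: "The CSQ will be completed by the SDM if the patient is not able to complete it". Table 2 schedules the QOL-AD at T1, T2 and T3 with repeated measures ANOVA, and the CSQ at T3 only with descriptive statistics and content analysis.

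**Who measures.** For sit-to-stand time, the primary efficacy outcome, "the interventionist or RA will ask participants to stand from a seated position three times". The interventionist and RAs "measure the time to complete the sit to stand for participants until ≥75% interrater agreement is reached", after which: "Then only one RA or the interventionist will collect the rest of the outcome measures data". Outcome Data Collection Method is general: "T1, T2, and T3 data will be recorded on paper forms by the RA or interventionist".

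**Who delivers.** Under Intervention Components, "the interventionist will meet with participants for one session per day, 5 days per week".

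**Bias control.** Measures to be taken to Minimize Bias begins: "Research assistants will be hired and will be trained to collect data from older adults". It adds standardized procedures, valid tools and strict inclusion criteria. It contains no rule on respondents and does not separate the deliverer from the assessor.

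**The concern.** The study has one group, so research question 3 rests wholly on change within participants. Anything that differs systematically between T1 and T3 other than the participant's state goes straight into that change. Three arrangements are left open.

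- **QOL-AD respondent.** A patient who answers at T1 may be unable to at T3, or the reverse. The change then contains the difference between two raters. The population makes this plausible: the Inclusion criteria admit delirium and dementia, and the consent procedure provides for a patient who stops appearing alert and able to communicate.
- **CSQ respondent.** Research question 2 asks about the older adults' satisfaction, and the hypothesis is a score of 3 or more on all items. An SDM's answer is another person's view. The consent section expects that some SDMs or care partners cannot be onsite, so an SDM may not have seen a session.
- **Deliverer as assessor.** The person who has worked with the participant five days a week may hold the stopwatch and collect the questionnaire that rates those sessions.

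**Working it through.** **1. The plan's own figure.** Inputs from Sample Size: f = 0.25, alpha = 0.10, power 0.8, three measurements, correlation 0.6, nonsphericity 0.8. With λ = f²·N·m·ε/(1−ρ), df1 = (m−1)ε and df2 = (N−1)(m−1)ε, power is 0.792 at N = 20 and 0.811 at N = 21. The stated 21 is reproduced. For attrition just under 20%, 21/(1−0.19) = 25.9, which rounds up to the stated 26. The sample size is not in dispute.

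**2. Passages side by side.**

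| Measure | Times | Permitted respondent or assessor | What is not fixed |
|---|---|---|---|
| QOL-AD | T1, T2, T3 | Patient or SDM | Same respondent throughout |
| CSQ | T3 | Patient or SDM | Separate reporting |
| Sit-to-stand time | T1, T2, T3 | Interventionist or RA | Exclusion of the deliverer |
| Other T1–T3 data | T1, T2, T3 | RA or interventionist | Exclusion of the deliverer |

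The agreement step covers sit-to-stand time only.

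**3. Effect of QOL-AD switches on mean change.** The Protocol gives neither a switch rate nor a self–proxy gap, so both are assumed. If k of 21 completers switch between T1 and T3, all in the same direction, and raters differ by d points, the mean change shifts by k·d/21.

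| k | d = 2 | d = 6 | Share of 3-point criterion |
|---|---|---|---|
| 4 | 4×2/21 = 0.38 | 4×6/21 = 1.14 | 13% to 38% |
| 8 | 8×2/21 = 0.76 | 8×6/21 = 2.29 | 25% to 76% |

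Switches in opposite directions would partly offset one another in the mean. In each participant who switches, the full gap d enters that person's change.

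**4. Effect on the test.** Repeated measures ANOVA was simulated with n = 21, correlation 0.6, alpha 0.10 and no true change (10,000 runs per case). Without any shift the rejection rate is about 0.10.

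| Assumed shift at T3 | Rejection rate |
|---|---|
| 4 of 21 switch, gap 0.5 SD | 0.13 |
| 4 of 21 switch, gap 1 SD | 0.20 |
| 8 of 21 switch, gap 0.5 SD | 0.22 |
| 8 of 21 switch, gap 1 SD | 0.53 |
| Assessor shift in all participants, 0.1 SD | 0.13 |
| Assessor shift in all participants, 0.2 SD | 0.26 |
| Assessor shift in all participants, 0.3 SD | 0.44 |

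The Protocol gives no QOL-AD standard deviation, so these gaps cannot be converted into points.

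**5. What cancels.** If an assessor adds a lean b at every visit, change is (T3 + b) − (T1 + b) = T3 − T1, and b drops out. Only a lean that differs between visits biases change, for example through a different assessor or expectations that grow over the six weeks.

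**The case against.** **Assessor change is largely addressed.** A reader might infer that RA and interventionist may alternate freely. The agreement step followed by "Then only one RA or the interventionist will collect the rest of the outcome measures data" is most naturally read as one assessor after calibration. This stands, and limits assessor change. It does not exclude the deliverer from being that one person, and agreement between raters says nothing about expectation. The looser sentence under Outcome Data Collection Method should match it.

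**Visit-by-visit switching is not stated.** The Protocol does not say whether ability to complete the QOL-AD is judged once or at each visit. Switching is permitted, not prescribed.

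**The CSQ has no change to bias.** Correct: it is taken once. The issue there is pooling and proxy validity. Nor is its administration assigned to the interventionist; that is one of two permitted options. Open-ended questions and field notes supplement the score.

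**An RA is not a blinded assessor.** Also correct. Everyone knows the treatment and the time point, and under Potential risks an RA follows the participant with a wheelchair in the first week or longer. Using an RA removes the deliverer from assessment but does not blind it.

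**Some of this may sit elsewhere.** Separate analysis of self and proxy scores may be in an SAP, and the appended forms, which are not shown, may record who answered. Who answers and who measures are nonetheless data-collection rules, and the Protocol's own sentences on them leave the choice open.

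**Conclusion.** The point holds in limited form. As written, the plan lets self and proxy QOL-AD scores enter one within-person change, lets SDM and patient CSQs be pooled for a question about the patients, and lets the deliverer measure the outcomes although hired RAs are the stated bias control.

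The size is unknown. Under the assumed 4 switches in 21 and a gap of 2 to 6 points, mean QOL-AD change moves by about 0.4 to 1.1 points, in an unknown direction, against a criterion of 3. That alone would not reach the criterion, but it could help a result over it or hide a real gain. The rejection rates rest equally on assumed shifts.

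A reader might go further and conclude that the efficacy results will be biased upwards, or that the feasibility conclusion is unsafe. The Protocol supports neither. The direction of a respondent effect is not known, a constant assessor lean cancels, and recruitment, retention, adherence and the sample size do not depend on these rules. What is affected is interpretation of research question 3, mainly quality of life, and of satisfaction in research question 2.

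**What to change.** 1. **QOL-AD.** Choose the respondent at T1 and keep that respondent at T2 and T3 where possible. Where a switch occurs, keep the data and add a sensitivity analysis restricted to participants whose respondent did not change. Switched visits should not be set to missing: that would selectively drop participants who lost or regained the ability to self-report, and would trigger the paired t-test fallback that Plan for Analysis prescribes for missing data.
2. **CSQ.** Report patient-completed and SDM-completed questionnaires separately, and base research question 2 on the patient-completed ones.
3. **Assessor.** Amend the sit-to-stand text under Secondary Outcomes and the opening of Outcome Data Collection Method so that one trained RA, not the interventionist, does a given participant's T1 to T3 assessments and hands out the CSQ.
4. **Forms.** Record respondent and assessor at every assessment.

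**Cost.** Wording changes, two form fields and RA scheduling at three visits; RAs are already planned, so no new staff are needed. Fewer CSQs will count towards research question 2. The RA remains unblinded and may have accompanied early sessions, which the report should say.

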**Table 3: Checklist of Mobility-Related Services Provided**

| **Services** | **Yes** | **No** | **n/a** | **Comment (specify dose where appropriate)** |
| --- | --- | --- | --- | --- |
| Mobility |  |  |  | Daily/weekly/bi-weekly/other: please specify |
| Rehabilitation training including transfers, stairs, strength and balance exercises and provision of mobility aids |  |  |  | Daily/weekly/bi-weekly/other: please specify |
| Functional training in ADL (toileting, washing, dressing, walking) |  |  |  | Daily/weekly/bi-weekly/other: please specify |
| Psychosocial care measures such as central dining, recreational activities, group exercises, spiritual care |  |  |  | Daily/weekly/bi-weekly/other: please specify |

**Outcome Data Collection Method**

T1, T2, and T3 data will be recorded on paper forms by the RA or interventionist and will be entered on at least a weekly basis into a secure one drive storage database hosted in an iDAPT network for the EnCOAR Team (TRI-UHN), which has restricted access and safety backup. Data on intervention fidelity and adherence will be collected on paper forms by the interventionist immediately after each session with the participants and will be transcribed onto the one drive on a weekly basis.

**Measures to be taken to Minimize Bias**

Research assistants will be hired and will be trained to collect data from older adults and the procedures will be standardized to minimize bias. Reliable and valid measures have been selected and have well established outcome measures to minimize biases. Patients are selected to participate based on strict inclusion criteria which will minimize sampling bias.

**Plan for Missing Data**

A plan to minimize the risk of missing data will be put in place. Specifically, an Ethical Protocol and Algorithm for Data Collection and Intervention Session: Procedure for Assessing Assent and Dissent for the OASIS Walking Intervention (Appendix J) will be used. This protocol is adapted from the Ethic Protocol used by Chu and colleagues (23). For their study, all follow up assessments were completed and there was no missing data (23). This protocol includes establishing rapport with participants, obtaining assent prior to initiating data collection, and re-approaching if the participant initially refuses (Appendix J). Data on paper sheets will also be visually inspected for missing data prior to transferring them onto the secure One drive. In addition to the above retention strategy, remuneration will also be provided to reduce the risk of drop out and thus reduce the risk of missing data (see remuneration, section 7.4)

# STATISTICS

**Sample Size**

An activity-based study involving older adults with dementia in the nursing home setting (31) that used time to perform one sit to stand found a moderate effect size (Cohen’s d) of 0.48. Since the present study will use repeated measures ANOVA, a Cohen’s *f* of 0.25 (a suggested value for moderate effect size) (55) was used in the sample size calculation. Based on an *f* of 0.25, a power of 0.8 and an alpha of 0.1, in keeping with those used in a mobility study involving older adults with dementia (23), a sample of 21 participants will be needed for this study. Using an alpha of 0.1 can be acceptable for exploratory or preliminary studies (56) (p. 188). An attrition rate of just under 20% over the course of a 6-week study will be taken into account, as was experienced in a 6-week intervention study involving older adult residents with dementia (28). Thus, a sample of 26 participants will be recruited for this study. G*Power 3.1.9.7 software (57) was used for the sample size calculation for an ANOVA: Repeated measures, within factors statistical test with one group, three measurements, 0.6 for the correlation among repeated measures, and 0.8 for nonsphericity correction (which is a mild departure from sphericity) (56).

The sample size is achievable based on input provided by our collaborating TCP administrators, as the TCP has a 35-bed capacity and most patients have cognitive impairment.

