**Literature Review**

A comprehensive search of the literature involving mobility interventions led by nurses yielded: zero studies in the TCP setting; six studies with significant results involving older adults with cognitive impairment and walking interventions that were led by nurses or that could be done by nurses in the nursing home setting (23-30); and one study with significant results involving sit to stand activity in the nursing home setting (31).

In nursing homes, walking had a typical dose of 30 minutes per session (24, 25, 28-30), ranged from two (23) to seven (27) sessions per week; and duration ranged from six weeks (28) to six months (29). Overall, the most effective intervention was administered by a nurse and involved 2-4 walking sessions per week for 4 months and incorporated a person-centered communication care plan (23). This study had the highest recruitment and adherence rates, monitored intervention fidelity, and resulted in a significant improvement to all outcomes (functional mobility, activities of daily living function, and quality of life).

One study done in nursing homes involving older adults with dementia found that doing sit to stands 6 sit to stands per day resulted in maintained mobility (measured by the amount of time to perform one sit-to-stand) (p=0.01), which can also be a measure of lower extremity muscle strength (31).

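### The sample size cites d = 0.48 as its empirical basis but enters f = 0.25 unconverted; over three visits that f corresponds to a larger difference, about 0.53-0.61 SD

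*Protocol*

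**What the plan says.** The Sample Size section refers to an activity-based study in nursing home residents with dementia "that used time to perform one sit to stand found a moderate effect size (Cohen’s d) of 0.48". Because the analysis will be a repeated measures ANOVA, the section then takes a Cohen's f of 0.25, "a suggested value for moderate effect size) (55) was used in the sample size calculation". With "a power of 0.8 and an alpha of 0.1", one group, three measurements, a correlation of 0.6 and a nonsphericity correction of 0.8, it concludes that "a sample of 21 participants will be needed for this study". On attrition it says "An attrition rate of just under 20% over the course of a 6-week study will be taken into account", and so "a sample of 26 participants will be recruited for this study".

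Time to one sit-to-stand is the outcome named first for efficacy (Secondary Outcomes). The analysis section plans an omnibus repeated measures ANOVA over T1, T2 and T3, followed by pairwise comparisons if the F test is significant.

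**The concern.** The values 0.48 and 0.25 are linked only by the label moderate. They are on different scales: d is a difference between two means, while f is the spread of all the means around their average. Passing from one to the other needs a conversion that depends on the number of means and their pattern, and none is shown. If the converted f is smaller than 0.25, the design has less power at the effect put forward as its basis than a reader would take from the section. A non-significant F for sit-to-stand time would then be weighed against a power that belongs to a larger effect.

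**Working it through.** **Inputs, all from the Sample Size section:** d = 0.48; f = 0.25; alpha = 0.10; target power 0.80; m = 3 measurements; correlation ρ = 0.6; nonsphericity ε = 0.8; n = 21 completers; 26 recruited. Two things are not given: the SD that scales the 0.48, and whether the 0.48 is a between-group or a pre-post contrast.

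**Formula** (one-group within-factor repeated measures ANOVA, noncentral F):
- λ = f² × n × m × ε / (1 − ρ) = f² × n × 3 × 0.8 / 0.4 = 6 n f²
- df1 = (m − 1)ε = 1.6; df2 = (n − 1)(m − 1)ε = 1.6(n − 1)

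**Step 1: reproduce the plan.** With f = 0.25:
- n = 20: λ = 6 × 20 × 0.0625 = 7.50, power 79.2%
- n = 21: λ = 6 × 21 × 0.0625 = 7.875, power 81.1%

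So 21 is the smallest n reaching 80%, as stated. For attrition, 21 / (1 − 0.19) = 25.9, which rounds up to 26 and agrees with a loss of just under 20%.

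**Step 2: convert d to f for three means.** The correlation enters λ separately, so f has to be in units of the common SD of the scores. Let the largest difference among the three means be d.
- Equal steps (0, d/2, d): the deviations from the average are −d/2, 0 and d/2, so f = d/√6 = 0.48 / 2.449 = 0.196. This is the minimum.
- All change by one visit, then held (0, d, d): f = d√8/6 = 0.48 × 0.4714 = 0.226. This is the maximum.

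No pattern of three means with a largest difference of 0.48 reaches 0.25.

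**Step 3: run it backwards.** The largest difference that corresponds to f = 0.25 is 0.25 × 6/√8 = 0.53 (maximum pattern) to 0.25 × √6 = 0.61 (equal steps). That is 10% to 28% above 0.48.

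**Step 4: power at d = 0.48 in common-SD units.**

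| f | Power, n = 21 | Power, n = 26 | Completers for 80% |
|---|---|---|---|
| 0.196 | 62.3% | 71.2% | 33 |
| 0.226 | 73.6% | 82.1% | 25 |
| 0.25 (as planned) | 81.1% | 88.5% | 21 |

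**Step 5: sensitivity to the scaling of 0.48.** If it was divided by the SD of change, then with ρ = 0.6 that SD is √(2 × 0.4) = 0.894 of the score SD. The effect in score-SD units is 0.48 × 0.894 = 0.43, f is 0.175-0.202, and power with 21 completers is 53.9% to 64.8%. If 0.48 is a between-group contrast, no f for a one-group design follows from it without a further assumption about the within-person change.

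**Step 6: a single T1-T3 comparison** (paired t test, two-sided alpha 0.10, n = 21). On the score-SD scale the standardised change is 0.48 / 0.894 = 0.537 and power is 76.7%. On the change-SD scale it is 0.48 and power is 68.4%.

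**The case against.** The strongest reply is that nothing was miscalculated. The section states its power for f = 0.25, says openly that this is a suggested value, and the resulting 21 reproduces. That stands. A reader might infer that the software calculation is wrong, or that the protocol claims 80% power at d = 0.48. The document supports neither. The fault is that 0.48 is presented as the basis and a larger effect is then used.

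A second reply is that 62-74% depends on a definition of 0.48 that the protocol does not give. That also stands, so the range must be stated conditionally. The change-SD reading does not rescue the plan, because it lowers power. The two-mean shortcut f = d/2 = 0.24 would give 78.1% with 21 completers, but it does not apply to three visits and still falls short of 0.25.

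A reader might also infer that the cited study showed no gain at all, because the Literature Review says its activity "resulted in maintained mobility (measured by the amount of time to perform one sit-to-stand". The document does not settle this. The Study Hypotheses cite the same study for a reduction of at least 0.87 seconds in sit-to-stand time. The two descriptions differ and the source is not at hand, so no argument should rest on maintenance alone.

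Third, feasibility is the primary outcome, the relaxed alpha is defended as suitable for early-stage work, and no progression rule hangs on a non-significant efficacy test. This limits the consequence but does not make the justification correct.

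**Conclusion.** Wrong as written, with low consequence. The sample size is right for f = 0.25, but f = 0.25 is not what d = 0.48 supports over three visits. With 21 completers the design has the planned power for a largest difference of about 0.53-0.61 SD. At 0.48 it has about 62-74% if 0.48 is the largest difference among the three means in common-SD units, and about 54-65% if 0.48 is scaled by the SD of change. If all 26 complete, the common-SD range becomes 71-82%. These figures take the plan's correlation, nonsphericity correction and alpha as given. That f = 0.25 exceeds the cited effect holds under both scalings; the exact size of the shortfall depends on information the protocol does not give. The finding is no ground for enlarging a feasibility study.

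**What to change.** Keep 26 participants and revise the Sample Size text to say four things:
- f = 0.25 is a conventional value and not a conversion of d = 0.48.
- 21 completers give 80% power only for a largest difference among the three visits of about 0.53-0.61 SD, depending on the pattern of change.
- At d = 0.48 in common-SD units, power with 21 completers is about 62-74%.
- Which SD and which contrast the 0.48 refers to. If it was scaled by the SD of change, quote 54-65% instead.

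The cost is a few sentences and a less favourable power statement, with no additional patients.

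Optionally, the T1-T3 contrast could be pre-specified as the main efficacy test, with about 77% power at d = 0.48 on the score-SD scale or 68% on the change-SD scale. That would change the planned analysis as well as the wording, so it is a separate decision and is not needed to correct this point.
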